## Abstract

**Background:**

Thrombolysis with intravenous rt-PA is currently the only approved acute therapy for ischemic stroke. Re-occlusion after initial recanalization occurs in up to 34% in patients treated with rt-PA, probably caused by platelet activation. In acute myocardial infarction, the combination of thrombolysis and antiplatelet therapy leads to a greater reduction of mortality compared to thrombolysis alone. In patients with acute ischemic stroke, several studies showed that patients already on antiplatelet treatment prior to thrombolysis had an equal or even better outcome compared to patients without prior antiplatelet treatment, despite an increased risk of intracerebral bleeding. Based on the fear of intracerebral haemorrhage, current international guidelines recommend postponing antiplatelet therapy until 24 hours after thrombolysis. Remarkably, prior use of antiplatelet therapy is not a contra-indication for thrombolysis. We hypothesize that antiplatelet therapy in combination with rt-PA thrombolysis will improve outcome by enhancing fibrinolysis and preventing re-occlusion.

**Methods/Design:**

ARTIS is a randomised multi-center controlled trial with blind endpoint assessment. Our objective is to investigate whether immediate addition of aspirin to rt-PA thrombolysis improves functional outcome in ischemic stroke. Patients with acute ischemic stroke eligible for rt-PA thrombolysis are randomised to receive 300 mg aspirin within 1.5 hours after start of thrombolysis or standard care, consisting of antiplatelet therapy after 24 hours. Primary outcome is poor functional health at 3 months follow-up (modified Rankin Scale 3 - 6).

**Discussion:**

This is the first clinical trial investigating the combination of rt-PA and acute aspirin by means of a simple and cheap adjustment of current antiplatelet regimen. We expect the net benefit of improved functional outcome will overcome the possible slightly increased risk of intracerebral haemorrhage.

**Trial registration:**

The Netherlands National Trial Register NTR822. The condensed rationale of the ARTIS-Trial has already been published in Cerebrovascular Diseases.

## Background

Stroke is an important cause of death and acquired disability in industrial world. In the large majority of ischemic strokes, cerebral arteries become occluded either by a cardiac embolus or by thrombus formation in atherosclerotic vessel walls. The process of thrombus formation is initiated by two separate but interacting mechanisms: fibrin formation and platelet activation. Current standard treatment in acute ischemic stroke with intravenous recombinant tissue plasminogen activator (rt-PA) aims at breaking down the fibrin cloth in order to restore recanalisation of the occluded artery. Rt-PA treatment results in an absolute 10% reduction of poor outcome compared to placebo [1]. However, benefit from this treatment rapidly declines over time after symptom onset. The number needed to treat to have 1 patient with favourable outcome is 4-5 if treatment is started within 90 minutes after symptom onset as compared to controls [2], while this number increases to 14 if treatment is started between 3 to 4.5 hours after symptom onset [2,3].

Within this current time window, early recanalisation is strongly associated with improved functional outcomes and reduced mortality [4,5]. Unfortunately, recanalisation with intravenous rt-PA is only modest. The overall recanalisation rate observed in 14 pooled intravenous thrombolysis studies was only 43% [5], partly due to re-occlusion. In continuous transcranial Doppler monitoring studies, re-occlusion occurs in 20 - 34% of rt-PA treated patients at a mean time of 65 minutes after start of treatment [6,7]. Moreover, these studies show that re-occlusion accounts for two thirds of the observed clinical deterioration after initial improvement. A recent study confirmed the association between re-occlusion and clinical deterioration and showed that early re-occlusion is highly predictive of long-term poor outcome [8].

Re-occlusion after initial recanalisation is probably initiated by increased platelet activation. Thrombolytic therapy strongly activates the coagulation cascade leading to thrombin formation, a potent platelet activator [9]. This haemostatic activation is maximal at 2 hours after initiation of rt-PA treatment [10]. Exposure of the lipid core of a disintegrating thrombus also leads to increased platelet aggregation. These activated platelets induce secretion of plasminogen activator inhibitor-1, which has been shown to be the responsible factor in t-PA resistance to lysis in platelet rich arterial thrombi [11].

Among all antiplatelet drugs, aspirin (acetylsalicylic acid) is the most widely used drug. Inhibition of platelet aggregation by aspirin is caused by the irreversible acetylation of cyclo-oxygenase 1 and inhibition of prostaglandin thromboxane A2. Aspirin has a rapid onset of action resulting in substantial elimination of activated platelets.

In myocardial infarction, large clinical trials have shown that adding aspirin to thrombolysis prevents re-occlusion thereby improving outcome considerably. The results of the second International Study of Infarct Survival Trial (ISIS-2) showed that mortality was reduced by 42% if patients were treated with streptokinase in combination with aspirin while mortality was reduced by only 25% if patients were treated with streptokinase alone [12]. Aspirin is therefore the standard adjunctive treatment in acute myocardial infarction.

In acute ischemic stroke, the Multicenter Acute Stroke Trial - Italy (MAST-I) duplicated the design of the ISIS 2 and showed an absolute risk reduction of 14% for disability in patients treated with the combination of streptokinase and aspirin as compared streptokinase alone. This overall net benefit overcame an excess mortality rate which was observed in the combination group. Symptomatic intracerebral haemorrhages (SICH) largely contributed to this increased mortality rate [13]. Meta-analysis of the streptokinase trials confirmed a positive effect on functional outcome with concomitant use of aspirin that compensated for higher mortality rates [14]. Besides the high dosage of streptokinase used in these trials, its non-fibrin-selectivity is nowadays generally held responsible for the high number of SICH observed in this study.

The addition of aspirin to rt-PA, which is a fibrin-selective thrombolytic agent, has never been investigated prospectively. In the protocol of the Neurological Institute of Neurological Disorders and Stroke (NINDS) Trial the use of antiplatelet agents was postponed for 24 hours after rt-PA treatment to prevent possible bleeding complications [15]. However, the protocol did allow enrolling patients already on antiplatelet drugs. Current guidelines adopted these trial criteria for fear of SICH [16].

Subgroup analysis of the NINDS-trial reveals that patients with prior aspirin use had a better outcome, with lower frequencies of clinical deterioration and the same SICH rate as compared to patients without previous aspirin use [17]. Regarding the association between clinical deterioration and the occurrence of vessel re-occlusion in ischemic stroke [6,8] and the lower incidence of clinical deterioration in patients with antiplatelet pre-treatment [17], one might suggest that previous antiplatelet therapy prevents re-occlusion. This hypothesis is supported by the observation from recent prospective cohort studies, which confirm this favourable outcome after thrombolysis in patients with prior use of antiplatelet drugs [18,19]. Based on all these observations we hypothesize that immeditate addition of antiplatelet therapy to rt-PA in acute ischemic stroke improves outcome by enhancing clot lysis and preventing re-occlusion after initial recanalisation.

## Methods and Design

### Study design and objective

The Antiplatelet therapy in combination with Recombinant t-PA Thrombolys in Ischemic Stroke (ARTIS) Trial is a multi-center, prospective open, randomised controlled trial with blind endpoint assessment (PROBE-design). We compare direct addition of 300 mg aspirin to intravenous rt-PA thrombolysis for ischemic stroke versus standard thrombolysis care, in which antiplatelet drugs are usually delayed by 24 hours after rt-PA. All participating centres are experienced in thrombolytic treatment for acute stroke.

The primary objective of the ARTIS-Trial is to investigate whether the addition of asprin to standard rt-PA thrombolysis reduces poor outcome in acute ischemic stroke. Poor outcome is defined as death or dependency assessed by the modified Rankin Scale (mRS, score 3-6) at 3 months follow-up.

### Enrolment procedures

The study population are acute ischemic stroke patients who present at participating centres and are treated with intravenous (IV) thrombolysis with rt-PA. Patients aged 18 years or older can be enrolled. Patients will be asked for written informed consent. The trial itself has no other firm exclusion criteria than those established by the judgment of the individual treating physician using local protocols for IV rt-PA treatment. When the patient has a diminished decision-making capacity as result of the stroke (e.g. aphasia), informed consent will be obtained from a representative of the patient. Exclusion of these patients would lead to a selective patient sample. Patients are also excluded if they have:

▪ known antiplatelet therapy in the previous 5 days (in case of uncertainty the patient may be included);

▪ known thrombocytopenia or thrombocyte count < 100 * 10E9/l;

▪ known contra-indications to acetylsalicylic acid treatment;

▪ known anticogualant therapy in the previous 5 days;

▪ known legal incompetence of the patient prior to this stroke.

### Randomisation

Randomisation will be performed per participating centre to ensure a equal distribution of patients between both group. The randomisation procedure will be computer- and web based, using permuted blocks. Randomisation will be stratified by centre, age (≤ 60 years, > 60 years), gender and the time between symptom onset and time of rt-PA bolus (< 2 hours, 2-3 hours, > 3 hours).

### Intervention

In order to prevent delay of start of thrombolytic treatment, informed consent and randomisation procedures will be performed as soon as continuous infusion of rt-PA (0.9 mg/kg) has started after bolus administration (10%) Patients allocated to the active group will receive 300 mg aspirin (Aspégic^®^) as lysine salt intravenous as bolus. Since there is a peak in platelet activation after 2 hours after initiation of rt-PA thrombolysis [10], aspirin will be administered within 1.5 hours after the rt-PA bolus. Patient and treating physician are not blinded for treatment allocation.

We choose to apply aspirin intravenously for two reasons. First, onset of action has to be as soon as possible as re-occlusion starts to occur soon after rt-PA administration [6,7]. Intravenous aspirin leads to faster platelet suppression than oral aspirin, which results in a widely varying uptake [20]. Aspirin may be given simultaneous with the rt-PA continuous infusion, preferably through a different intravenous line. In case of only one intravenous access, rt-PA infusion has to be shortly interrupted in order to administer aspirin through this line with saline flushing before and afterwards.

Second, intravenously administration enables patients having swallowing difficulties caused by their stroke to be included. Exclusion of this subgroup would make the trial prone to inclusion bias.

### Investigational medicinal product

Aspirin intravenous is registered in the Netherlands as Aspégic^® ^(Sanofi-Synthelabo BV). Thrombocyte aggregation is irreversibly reduced by this calcium-ureum-salt, causing longer coagulations times. Aspirin use may lead to gastro-intestinal reactions. However, due to the single use adverse reactions caused by the trial medication are expected to be limited.

Alteplase^® ^(Boehringer Ingelheim GmbH) is essential and important co-medication in the ARTIS-Trial. Interaction of Aspégic^® ^with rt-PA is unknown, although rt-PA treatment might increase the risk of intracerebral bleeding in aspirin pre-treated stroke patients. The characteristics of rt-PA may therefore influence our results even though rt-PA itself is not under investigation.

### Recommendations concerning rt-PA treatment

Patients will receive rt-PA treatment in both groups according to local protocols at participating centres. Recommendations of rt-PA treatment concerning hypertension and thrombocyte count are based on standard international guidelines [16]. Blood pressure should not be lowered with medication prior to rt-PA treatment. If during rt-PA administration blood pressure rises above 180 mmHg systolic or 105 mmHg diastolic it is recommended to administer 10 mg labetalol intravenous within 1-2 minutes. This should be repeated every 10-20 minutes until blood pressure is below 180 mmHg systolic or below 105 mmHg diastolic. 150 mg labetalol is the maximum doses in 24 hours. During this treatment blood pressure should be measured every 15 minutes. If the blood pressure does not respond to labetalol, iv nitroprusside 0,5-10 μg/kg/minute should be added, with continuous blood pressure monitoring. In case the diastolic blood pressure is above 140 mmHg nitroprusside should be administered immediately as stated above. Thrombocyte count is not necessary before starting rt-PA treatment unless a patient is known with thrombocytopenia [21]. Deviations from these recommendations are not regarded as protocol violations, but will be registered.

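### The advisory labetalol stop rule joins its two limits with *or* where *and* is needed, so a reading with only one raised component, such as 200/100, meets both the start and the stop rule

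*Protocol article*

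**What the plan says.** The blood-pressure advice stands in one paragraph of the Protocol article, under Recommendations concerning rt-PA treatment. Its steps are:

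- **Start.** "If during rt-PA administration blood pressure rises above 180 mmHg systolic or 105 mmHg diastolic", give 10 mg labetalol intravenously.
- **Repeat and stop.** Repeat every 10-20 minutes "until blood pressure is below 180 mmHg systolic or below 105 mmHg diastolic", up to 150 mg in 24 hours.
- **Monitor.** "During this treatment blood pressure should be measured every 15 minutes".
- **Escalate.** "If the blood pressure does not respond to labetalol, iv nitroprusside" is to be added. Separately, "In case the diastolic blood pressure is above 140 mmHg nitroprusside should be administered immediately".

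The same paragraph sets the status of the advice: "Patients will receive rt-PA treatment in both groups according to local protocols at participating centres", and "Deviations from these recommendations are not regarded as protocol violations, but will be registered". The article does not restate the stop rule anywhere else.

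**The concern.** A start rule and a stop rule for the same drug should not both be true of one reading. The start rule fires if either component is too high, so treatment should end only when neither is. The stop rule is instead satisfied as soon as one component is under its limit. In a patient with an isolated systolic or isolated diastolic rise, the other component may be under its limit before the first dose. Followed literally, repeat labetalol could then cease while the raised component is still above its limit.

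The rule concerns blood pressure during the rt-PA infusion, when trial aspirin may be running as well (Intervention). The Discussion names SICH as a major safety concern, and it is a secondary outcome (Outcome measures) and a focus of the Data Safety Monitoring Board (Safety reporting). In that setting the start, stop and escalation steps should agree.

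**Working it through.** **Inputs.** All come from Recommendations concerning rt-PA treatment. S is systolic and D is diastolic pressure in mmHg.

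- Start: S > 180 or D > 105
- Stop as written: S < 180 or D < 105
- Stop with *and*: S < 180 and D < 105

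**Logic.** The negation of (S > 180 or D > 105) is (S ≤ 180 and D ≤ 105). Apart from the treatment of exact equality, the stop rule that matches the start rule therefore needs *and*.

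**The four combinations**, one example reading each:

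| Reading | Raised | Start met | Stop met, as written | Stop met, with *and* |
|---|---|---|---|---|
| 200/100 | systolic only | yes | yes | no |
| 170/110 | diastolic only | yes | yes | no |
| 200/110 | both | yes | no | no |
| 170/100 | neither | no | yes | yes |

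Start and stop overlap in 2 of 4 combinations as written and in 0 of 4 with *and*.

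**Check on a grid.** Take every whole-number reading with S from 120 to 230, D from 60 to 140 and S > D.

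- Both raised: 50 × 35 = 1750.
- Systolic raised and D < 105: 50 × 45 = 2250. Both rules are met.
- Diastolic raised and S < 180: 60 × 35 = 2100, less 231 pairs with S ≤ D, = 1869. Both rules are met.
- One component raised and the other exactly at its limit: 50 (D = 105) + 35 (S = 180) = 85. The start rule is met and the written stop rule is not.

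Readings that meet the start rule: 1750 + 2250 + 1869 + 85 = 5954. Readings that also meet the written stop rule: 2250 + 1869 = 4119. With *and*, the overlap is 0. These counts test the logic on an arbitrary grid and are not proportions of patients.

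**Boundaries.** 200/105 and 180/110 meet the start rule but not the written stop rule, so the fault does not touch them. With *and*, 180/100 and 170/105 meet neither rule, so a course already begun continues until pressure is strictly below both limits.

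**Do the other steps close the gap?**

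- Escalation depends on failure to respond to labetalol. The only labetalol target in the text is the stop rule, and by its literal terms 200/100 is already at target.
- Immediate nitroprusside applies only to diastolic pressure above 140, so it covers neither 200/100 nor 170/110.
- Measurement every 15 minutes yields readings but does not say what to do with a mixed one.
- The allowance for extra antihypertensives (Concomittant medication and secondary prophylaxis) is left to the treating physician and sets no target.

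**The case against.** The strongest reply is that the sentence is loose rather than wrong. It echoes the pattern of the start rule and can be read component by component: treat a systolic above 180 until it is below 180, and a diastolic above 105 until it is below 105. The paragraph supports this. Escalating for non-response makes little sense if a component that was never raised counts as success. A patient still at 200/100 also still exceeds the start threshold, and few clinicians would regard that patient as finished.

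The reply continues that the text is background care, the same in both arms and subordinate to local protocols. The article also says, under Study design and objective, that "All participating centres are experienced in thrombolytic treatment for acute stroke". No endpoint, sample size or analysis depends on the rule. The Discussion ties the SICH concern to combining aspirin with rt-PA and does not mention blood pressure control. Finally, centres work from a full protocol that is not shown and may be worded correctly.

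Most of this stands, and it limits the weight of the point. The component-by-component reading is probably what was meant. It does not make the sentence right, because the words give two separately sufficient conditions and nothing else in the article corrects them. Advisory status does not make the wording idle either. Deviations are to be registered, which requires knowing what the advice is. As written, one centre could register stopping at 200/100 as a deviation while another counts it as compliant.

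**Conclusion.** The stop rule is wrong as written. Two of the four combinations of raised and not-raised components meet both start and stop, and with *and* none does. This logical result needs no assumption beyond reading the sentence literally.

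The clinical size is unknown and probably small. How many patients had an isolated systolic or diastolic rise during infusion cannot be derived from the article, and no under-treatment is shown. The advice is the same in both arms, and no effect on bias, power or the primary analysis is claimed. This is a low-priority drafting correction. It is worth making because it is specific, costs almost nothing and concerns a treatment threshold in a trial with a named bleeding risk.

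**What to change.** In the stop rule under Recommendations concerning rt-PA treatment, replace *or* with *and*, so that labetalol is repeated until systolic is below 180 mmHg and diastolic is below 105 mmHg. Leave the start rule and both nitroprusside steps as they are.

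Check the full protocol held by the centres. If it has the same wording, send them the one-word clarification. If it does not, correct only the article. When the article was written, 361 of 800 patients had been included, 37 centres were randomising and further centres were invited, so a clarification could still be used.

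The cost is one word, plus a short notice if needed. The design, sample size and analysis do not change.

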### Concomittant medication and secondary prophylaxis

All medication used before the stroke may be continued, except anticoagulance. Standard secondary prophylaxis is recommended according to the following scheme:

▪ carbasalate calcium 300 mg - once/daily - 24 hours after rt-PA for 14 days

▪ carbasalate calcium 100 mg - once/daily - 14 days after rt-PA

▪ simvastatine 40 mg - once/daily - 0-24 hours after rt-PA

▪ dipyridamole 200 mg - twice/daily - 24 hours after rt-PA

Additional anti-diabetic or antihypertensive medication may be started as regarded appropriate by the treating physician.

### Outcome measures

The primary endpoint is poor functional health at 3 months defined as dependency or death (mRS 3 - 6).

The secondary objectives are:

▪ complications within 48 hours after randomisation including the occurrence of SICH and serious systemic bleeding. SICH is defined as CT-documented haemorrhage and a clinical deterioration leading to 4 or more points increase on the National Institute of Health Stroke Scale (NIHSS) as compared to the best score on the NIHSS since admission. Serious systemic bleeding is defined as a potentially life threatening bleeding which requires immediate medical intervention;

▪ neurological symptoms quantified by the NIHSS 7 - 10 days after randomisation or at discharge if the patient is discharged within 7 days;

▪ survival at 3 months;

▪ disability at 3 months assessed by the AMC Linear Disablility Scale;

▪ functional health at 3 months non-dichotomized (ordinal mRS);

▪ causes of poor outcome.

### Data collection

At baseline following patient characteristics are collected at each participating site: age, sex, ethnicity, medical history, pre-stroke medication, pre-stroke mRS, blood pressure, Glasgow Coma Scale (GCS), National Institutes of Health Stroke Scale (NIHSS), time of symptom onset, rt-PA bolus and (if applicable) trial medication, thrombocyte count and coagulation-International Normalized Ratio. Baseline CT-scans will be collected from participating centres and assessed blindly centrally at the coordinating centre for dens media sign, early ischemic changes and degree of leukoariosis by an independent blinded neuro-radiologist.

At follow-up, neurological deficits are assessed by the NIHSS at 7-10 days or at discharge, if this is before 7 days. Clinical deterioration, defined as a 4 or more points increase on the NIHSS, will be followed by CT-scan and registration as (serious) adverse events including possible cause by each participating site. This CT-scan will be assessed at the coordinating centre as well.

Primary outcome will be assessed by a blind research nurse from the clinical trial office of the coordinating centre, who will score the mRS by telephone using a structured interview. To increase the inter-observer reliability the number of research nurses will be limited to a maximum of three. Disability will be assessed by the same research nurse during the same telephone interview using the Amsterdam Linear Disability Scale [22]. See Additional file 1 for all data collection forms.

In patients with a poor outcome at three months, the Data Collection Committee composed of the investigators of the coordinating centre and the local investigator, judges whether this poor outcome is attributed to the initial ischemic stroke, reported adverse event or other causes.

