### Safety reporting

All adverse event reported by the subjects or observed by the treating physicians will be recorded. In case of serious adverse events (SAE), the principal investigator will be notified by email or telephone within 24 hours. The principal investigator subsequently reports SAE to the Data Safety Monitoring Board (DSMB). This is an independent committee of trial experts, who will focus on both safety monitoring and analysis of effectiveness on unblinded data. The DSMB will perform ongoing safety surveillances, especially with regard to the occurrence of serious adverse events in terms of SICH and serious systemic bleeding within 48 hours. The DSMB can recommend the Steering Committee of the ARTIS-Trial to terminate the trial when there is clear and substantial evidence of harm. All SAE will be reported to the central METC according to their requirements as well.

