### Statistical analyses

Baseline characteristics will be summarized using descriptive statistics. The main analysis of this trial consists of a single comparison between the trial medication groups of the primary outcome after three months (dichotomized Rankin score). The analysis will be based on the intention-to-treat principle. The effect size will be expressed in a relative risk (RR) estimates and absolute risk reduction (ARR). Additionally the primary outcome will be analyzed using multivariate logistic regression, adjusting (if necessary) for clinically relevant baseline imbalances. The differences between NIHSS, ALDS scores and non-dichotomized mRS will be analyzed using the two-group *t*-test, the Mann-Whitney test, linear regression and ordinal logistic regression, when appropriate. The remaining secondary outcomes will be analyzed using simple 2 × 2 tables and logistic regression. In all analyses, statistical uncertainty will be quantified via 95% confidence intervals.

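### The cause of a poor outcome, a listed secondary outcome, is judged partly by the local investigator in an open-label trial, and no masking is described

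*Protocol article*

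**What the plan says.** All references are to the protocol article.

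- **Outcome measures** ends its list of secondary objectives with "causes of poor outcome".
- **Data collection** fixes who is judged, who judges and the categories. The patients are described as "In patients with a poor outcome at three months". On the judges it says: "the Data Collection Committee composed of the investigators of the coordinating centre and the local investigator, judges whether this poor outcome is attributed". Three attributions are possible, namely "to the initial ischemic stroke, reported adverse event or other causes".
- **Intervention** states: "Patient and treating physician are not blinded for treatment allocation".
- **Study design and objective** calls the trial a "randomised controlled trial with blind endpoint assessment (PROBE-design").
- **Data collection** states blinding for the research nurse who scores the modified Rankin Scale (mRS) and for the neuro-radiologist who reads the baseline CT scans. It says nothing either way about the Data Collection Committee.
- **Safety reporting** says that for serious adverse events "the principal investigator will be notified by email or telephone within 24 hours".
- **Statistical analyses** provides: "The remaining secondary outcomes will be analyzed using simple 2 × 2 tables and logistic regression". It names no denominator for this outcome.

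**The concern.** Deciding whether a stroke patient is dependent or dead because of the index stroke, a reported adverse event or something else is a matter of opinion in many cases. A judge who knows that a patient received early aspirin may be readier to blame an adverse event. A judge who believes in the treatment may be readier to blame the stroke. The direction cannot be predicted, and a larger sample does not remove the error.

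The outcome bears on the trial's central argument. The article expects better function to outweigh some extra haemorrhage, and its Discussion leaves open how much haemorrhage linked to prior aspirin use matters clinically. A comparison of the causes of poor outcome would naturally be read as evidence on that trade-off. It should therefore have the protection that the design announces.

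**Working it through.** **1. Which assessments have stated blinding**

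| Assessment | Assessor | Blinding stated? |
|---|---|---|
| mRS at 3 months (primary) | Research nurse, by telephone | Yes |
| Disability scale at 3 months | Same nurse, same interview | Yes, by the same nurse |
| Baseline CT | Independent neuro-radiologist | Yes |
| Cause of poor outcome | Coordinating-centre investigators and local investigator | Not stated |

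The row without stated blinding calls for the most judgement.

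**2. What the judges are likely to know**

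- *Local investigator.* Patients and treating physicians know the arm, and the comparator is standard care. Sites also record the time of trial medication where it applies, an entry that by itself reveals the arm. Knowledge of the allocation is very probable, though the article does not say that the local investigator is the treating physician.
- *Coordinating-centre members.* The principal investigator receives serious adverse event notices. The article does not say that these show the allocation, so for these members the question is open.
- *Source data.* When a patient deteriorates, the open-label site registers a possible cause. The site thus supplies a causal label and later helps to judge it.

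**3. How many patients are judged**

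Inputs from Trial size: 400 per group, poor outcome 0.50 (control) and 0.40 (aspirin), two-sided 0.05, 80% power. These figures reproduce. The usual two-proportion formula gives 388 per group, or 408 with continuity correction, and 400 per group gives power 0.81. The confidence half-width is 1.96 × √(0.25/400 + 0.24/400) = 0.0686, against the stated 0.069.

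Expected poor outcomes: 0.50 × 400 = 200 and 0.40 × 400 = 160, together 360.

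**4. How sensitive the outcome is to a few shifted judgements (illustration)**

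The documents give no rate of adverse-event attribution. Assume 20 truly attributable cases per arm, counted over all randomised: 20/400 = 5.0% in each, ratio 1.00.

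- Four aspirin cases moved from adverse event to stroke: 16/400 = 4.0%, ratio 16/20 = 0.80.
- Eight aspirin cases moved from stroke to adverse event: 28/400 = 7.0%, ratio 28/20 = 1.40.

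These shifts are 4/160 = 2.5% and 8/160 = 5% of the aspirin poor outcomes. Nothing in the documents says that shifts of this size would occur.

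**5. Why the denominator should be stated**

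The ratio among poor outcomes only is (a/160)/(c/200) = 1.25 × (a/c), where a and c are the aspirin and control counts. It is therefore always 200/160 = 1.25 times the all-randomised ratio at the planning rates. With c = 20:

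| a | Ratio, all randomised | Ratio, poor outcomes only |
|---|---|---|
| 16 | 0.80 | 1.00 |
| 20 | 1.00 | 1.25 |
| 28 | 1.40 | 1.75 |

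**The case against.** **Blinded assessment is honoured where it counts.** A blinded nurse scores the primary outcome, and the same interview yields the ordinal mRS and the disability scale. Survival is objective. The cause of poor outcome is the last of six secondary objectives and is given no role in the sample size or in stopping. This stands, and it limits the severity. It does not explain why a listed outcome goes without the protection stated for others.

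**Bleeding harm is measured elsewhere.** Symptomatic intracerebral haemorrhage and serious systemic bleeding are separate secondary outcomes with their own definitions, and the data safety monitoring board follows them. Bleeding is not one of the committee's categories. This also stands: the comparison of bleeding between arms does not pass through this committee.

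**An article may leave masking to the full protocol.** This stands in part. The article itself fixes the committee's membership, including the local investigator, so that much is a stated choice rather than an omission.

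A reader might infer two stronger points:

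- *That the whole committee is unblinded.* The article does not say so. The inference is strong for the local investigator and weak for the coordinating-centre members.
- *That the analysis uses the wrong denominator.* The article does not say that either. Only a patient with a poor outcome can have a cause for it, so judging only those patients is natural. A two-by-two table over all randomised patients, with good outcomes as non-events, fits the analysis text. The denominator is a detail that an article may leave to a fuller document.

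**Conclusion.** The point holds for the masking of the attribution. A subjective secondary outcome is judged by a group that includes someone who very probably knows the arm, with no masking described, in a trial that announces blinded endpoint assessment. About 360 patients would be judged if the planning rates hold. The direction and size of any bias cannot be derived from the documents; the shifts shown in the working rest on an assumed 20 cases per arm.

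Severity is low to moderate. On the denominator the article contains no error, and the factor of 1.25 is only a reason to say which denominator will be used.

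**What to change.** 1. State whether the committee sees the allocation.
2. Let the local investigator write the case summary but take no part in the classification.
3. Remove the allocation and all trial-medication entries from the summary, and have the existing coordinating-centre members classify it.
4. Compare arms on each cause as a proportion of all randomised patients, with good outcomes counted as non-events. Keep any breakdown among poor outcomes descriptive.

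The cost is a small clerical effort to redact summaries and some loss of local clinical knowledge in the judgement. No extra patients, visits or assessments are needed. The protection is not complete: the possible cause of a deterioration is still registered by an open-label site, and a coordinating-centre member may know the arm from other sources. The report should say so.
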